### Allocation and blinding

The backend server will automatically randomise participants to the three groups, post eligibility screening. Block randomisation will be used with random block sizes of 3 and 6. Since all randomisation procedures will be computerised, allocation will be unbiased and research personnel will be blind to allocation. There is a risk that allocation will be revealed to research personnel for some participants during follow-up phone calls. The study information will inform participants that the trial is investigating digital support materials and that they will be randomised to receive different materials. In this way, participants will be blind to allocation since they are unaware of both how many groups there are and what the different groups will receive.

### Statistical methods

All analyses will be done keeping participants in the groups to which they were randomised (intention-to-treat). In addition to three-way contrasts, analyses will also be conducted contrasting the two intervention groups combined versus the control group.

Analyses will be done using both available data and imputation. Imputation will be done using multiple imputation with chained equations (generating 200 data sets using predictive mean matching).^73^ Bayesian inference will be used to estimate the parameters of the models.^74^ Inference will be carried out using Stan, and convergence will be reported using trace plots, R-hat statistics and effective sample sizes. For each coefficient of interest, we will report the marginal posterior probability of effect, and the median will be used as a point estimate of the magnitude of the effect. We will also report 95% compatibility intervals defined by the posterior distributions’ 2.5% and 97.5% percentiles.

#### Models for primary and secondary outcomes

Primary outcomes will be modelled using multilevel regression with participant-level adaptive intercepts and group-by-time interactions (2-month, 4-month and 8-month follow-up measures). Secondary outcomes are measured at 8 months only and will be analysed using regression models with a group covariate. Both primary alcohol consumption outcomes will be modelled using negative binomial regression, and so will the number of visits to emergency healthcare services. Logistic regression will be used for hazardous and risky alcohol consumption classification, and linear regression will be used for the combined consumption measure (AUDIT-C), alcohol-related consequences scores (SIP) and quality of life (PROMIS Global Health 1.2). Frequency of drinking, typical number of drinks consumed on a drinking day and alcohol-related injury will be modelled using ordinal regression. Models of primary outcomes will be adjusted for baseline measures of the outcome using a time-by-baseline interaction, and models of secondary outcomes will be adjusted for baseline measures of both primary outcomes. In addition, all models will be adjusted for age, sex, education and access to money on short notice (see online supplemental Appendix A). We will use Student’s t priors for the main intercepts and coefficients, and half-Student’s t priors for dispersion and error terms. All Student’s t priors will be centred at 0, have a scale of 2.5 and 3 df. We will use normal priors for adaptive intercepts with standard normal hyperpriors for the SD parameters (mean=0, SD=1).

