## Methods and analysis

To address the study objectives, we will conduct a three-arm (1:1:1), parallel groups, RCT. The study received ethical approval from the Swedish Ethical Review Authority (16 April 2024, Dnr 2024-01630-01) and was prospectively registered in the ISRCTN trial registry on 12 June 2024 (ISRCTN87600318). This protocol has been written following Standard Protocol Items: Recommendations for Interventional Trials (SPIRIT) guidelines.^49^ Recruitment started in February 2025 and is planned to not extend beyond February 2026.

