### Study setting, recruitment and eligibility criteria

Through social media (Meta-platform, including Facebook and Instagram) and web search engine (Google search) advertisements, we will target individuals in the general population of Sweden looking for help online to reduce their drinking. We will target keywords that relate to reducing alcohol consumption, such as ‘drinking less’, ‘how to reduce my drinking’, ‘cutting down on alcohol’. Individuals will show interest in the study by sending a text message to a dedicated phone number. They will immediately receive a response with a link to a web page presenting informed consent materials (see online supplemental Appendix A). To keep participants blinded to avoid research participation effects,^50^ we will frame the study as one in which digital materials designed to help individuals reduce their drinking are evaluated, but details of the interventions will not be disclosed. This raises ethical issues, as the control group will not immediately receive an evidence-based intervention but only digital information about alcohol and health. Instead, control group participants will, at the end of trial participation, receive the personalised intervention.^16^

Consenting participants will be asked to respond to a baseline questionnaire, which will also assess eligibility (see online supplemental Appendix B for the questionnaires used in the study). Individuals will be eligible to participate if they are aged 18 or older, have access to a mobile phone and are classified as drinking at risky levels according to current Swedish guidelines. Since this is an effectiveness trial, we will not exclude participants based on concomitant care or restrict the use of other support. Immediately after completing the baseline questionnaire, eligible participants will be randomly allocated to one of the three study groups.

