### Sample size

This trial will use a Bayesian sequential design to avoid under-recruitment and over-recruitment.^65^,^68^ Bayesian sequential designs use target criteria which are evaluated continuously as data are made available, and recruitment ends once the criteria are considered sufficiently fulfilled. Throughout the study period, we will model the primary outcomes according to the analysis plan, and regression coefficients representing the effect of allocation to enhanced tailored versus personalised intervention at the 4-month interval will be asserted against target criteria for benefit, harm and futility. Note that relative differences between groups are estimated as incidence rate ratios for primary outcomes. We will aim to have one criterion fulfilled per primary outcome measure. In the case of futility, two additional criteria will be considered where intervention groups are combined and contrasted against the control group. The criteria for ending recruitment are:

Weekly alcohol consumption benefit/harm: the posterior probability is greater than 95% that past week’s alcohol consumption is *less/greater* in the enhanced tailored intervention group versus the personalised intervention group.

Frequency of heavy episodic drinking benefit/harm: the posterior probability is greater than 95% that the number of episodes of heavy drinking is *fewer/more* in the enhanced tailored intervention group versus the personalised intervention group.

Weekly alcohol consumption futility: the posterior probability is greater than 95% that the relative difference in past week’s alcohol consumption between the enhanced tailored intervention group versus the personalised intervention group is less than 15%.

Frequency of heavy episodic drinking futility: the posterior probability is greater than 95% that the relative difference in the number of episodes of heavy drinking between the enhanced tailored intervention group and the personalised intervention group is less than 15%.

In case of futility—benefit/harm versus controls: the posterior probability is greater than 95% that past week’s alcohol consumption is *less/greater* and number of episodes of heavy drinking are *fewer/more* in the intervention groups combined versus controls.

In case of futility—futility versus controls: the posterior probability is greater than 95% that the relative difference in both primary outcome measures between the combined intervention groups and the controls is less than 15%.

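### Each primary-outcome model leaves out the other primary outcome's baseline, which is already collected; adding it is an optional gain in precision, roughly 0–8% of variance under assumed correlations

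*Protocol article*

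**What the plan says.** The covariates are fixed in the protocol article under Models for primary and secondary outcomes. For the primary outcomes: "Models of primary outcomes will be adjusted for baseline measures of the outcome using a time-by-baseline interaction". For the secondary outcomes: "models of secondary outcomes will be adjusted for baseline measures of both primary outcomes". Four background covariates enter both kinds of model, since "all models will be adjusted for age, sex, education and access to money on short notice". So a primary model holds its own baseline by time plus four further covariates, and a secondary model holds both primary baselines plus the same four.

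On model form, "Primary outcomes will be modelled using multilevel regression with participant-level adaptive intercepts and group-by-time interactions" at 2, 4 and 8 months, and "Both primary alcohol consumption outcomes will be modelled using negative binomial regression".

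Both baselines are known before allocation: "Consenting participants will be asked to respond to a baseline questionnaire, which will also assess eligibility". Under Sample size, the 4-month coefficient for enhanced tailored versus personalised intervention is held against criteria for benefit, harm and futility, so the primary models decide when recruitment stops. The article gives no reason for the smaller baseline set in those models and no correlation between the two measures.

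**The concern.** The two primary measures view usual drinking through different windows: one sums the past seven days, the other counts heavy episodes over the past month. Eligibility follows the Swedish guideline, which is met by either weekly volume or monthly heavy sessions. Someone can therefore enter on heavy episodes after a light week. For that person, last week's count is a poor marker of usual drinking, and the heavy-episode baseline may predict later weekly drinking beyond it. The reverse can hold for heavy episodes.

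Two things are at stake, both modest. The first is precision in the models that drive stopping. The second is missing data. The article expects attrition to be a major limitation and plans an available-data analysis, which relies on missingness being random given the covariates and the observed outcomes. A further baseline drinking measure, plausibly related to both dropout and outcome, makes that somewhat more credible.

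**Working it through.** **The plan's own figure.** Under Sample size, the article expects 1750–2200 participants, from simulations with a 15% difference in weekly consumption. The code is in an appendix that is not shown, and the mean, dispersion and attrition are not given, so the figure cannot be reproduced. As a plausibility check, take n per arm = 2(1/μ + k)·((z₀.₉₅ + z_power)/ln 0.85)². With assumed μ = 12 drinks, k = 0.7, 90% power and 20% attrition:

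- ln 0.85 = −0.1625
- n = 2 × (0.0833 + 0.7) × (2.926/0.1625)² ≈ 508 per arm
- three arms: 1524; divided by 0.8: 1905

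Other assumed inputs give about 990 to 4300. The stated range is attainable but not verifiable.

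**Algebra of the gain.** Let r_own be the correlation of follow-up with its own baseline, r_x that with the other baseline, and r_b that between the two baselines. Then R²_own = r_own², R²_both = (r_own² + r_x² − 2·r_own·r_x·r_b)/(1 − r_b²), and the variance cut is 1 − (1 − R²_both)/(1 − R²_own). All correlations are assumed.

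- r_own 0.5, r_b 0.6, r_x 0.3: R²_both = 0.16/0.64 = 0.25, cut 0%. Here r_x = r_own × r_b, so the second baseline adds nothing.
- r_own 0.5, r_b 0.5, r_x 0.4: R²_both = 0.21/0.75 = 0.28, cut 4.0%.
- r_own 0.5, r_b 0.4, r_x 0.4: R²_both = 0.25/0.84 = 0.298, cut 6.3%.

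Over the whole grid (r_own 0.4–0.6, r_b 0.4–0.7, r_x 0.2–0.5) the cut runs from 0% to about 15%. The largest values sit at corners, such as the other baseline predicting as well as the outcome's own (0.5, 0.4, 0.5: 14.3%).

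**Count simulation.** Single-time-point negative binomial regressions, 1300 participants in two arms (about two thirds of 1975, the midpoint of 1750–2200, given a "three-arm (1:1:1), parallel groups, RCT"), 60 replicates per setting. Assumed: baseline means 14 and 6, follow-up means 11 and 5, rate ratio 0.85, SD of the stable log-rate 0.7, occasion SD 0.4, residual dispersion 0.15, baselines entered as log(1 + count). The correlation of weekly follow-up with its own baseline came out at 0.52–0.53. Mean standard errors of the group effect:

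| Correlation of the two baselines | Outcome | No baseline | Own | Both | Variance cut, own to both |
|---|---|---|---|---|---|
| 0.15 | Weekly drinks | 0.0508 | 0.0434 | 0.0433 | 0.6% |
| 0.15 | Heavy episodes | 0.0544 | 0.0483 | 0.0482 | 0.6% |
| 0.25 | Weekly drinks | 0.0511 | 0.0435 | 0.0431 | 1.9% |
| 0.25 | Heavy episodes | 0.0548 | 0.0486 | 0.0481 | 2.2% |
| 0.35 | Weekly drinks | 0.0509 | 0.0435 | 0.0426 | 3.9% |
| 0.35 | Heavy episodes | 0.0547 | 0.0484 | 0.0473 | 4.6% |
| 0.43 | Weekly drinks | 0.0508 | 0.0435 | 0.0421 | 6.3% |
| 0.43 | Heavy episodes | 0.0546 | 0.0482 | 0.0463 | 7.6% |

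(The percentages come from unrounded standard errors.) For comparison, own baseline against none in the first two rows: 1 − (0.0434/0.0508)² = 27% and 1 − (0.0483/0.0544)² = 21%. Most of the available gain is already in the plan.

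**Two further checks of the same kind.** A simulation with 900 participants in two arms and 300 data sets gave empirical SDs of 0.0599 (own, logged) and 0.0579 (both, logged). The ratio is (0.0579/0.0599)² = 0.934, a cut of about 7%. Its Monte Carlo range is roughly 1% to 12%. A simulation that applied the either-or eligibility rule gave 0.5–3% for weekly drinks and 0.4–2.6% for heavy episodes.

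**In participants.** Scaling 1750–2200 in proportion to variance, a 0.6% cut gives about 1740–2187 (10 to 13 fewer) and a 7.6% cut gives about 1617–2033 (133 to 167 fewer). This is a rough guide, since stopping depends on posterior criteria and not on a fixed variance.

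**The case against.** The strongest reply is that this is a preference. Own-baseline adjustment is standard, and the differing covariate sets need not be an inconsistency: the secondary outcomes are adjusted for the primary baselines rather than their own, whereas each primary outcome has its own natural baseline. That stands, and it is why the point is optional.

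Several other objections also stand. The simulations contain none of the four further covariates, no participant-level intercepts and only one time point, so they do not measure the exact increment over the planned model. Multiple imputation is planned as well, and the other baseline can enter there as a predictor, so the missing-data benefit falls mainly on the available-data analysis. The article says resources suffice if the sample must be larger, so the practical consequence is small. Recruitment has begun, so the change is not free of procedure.

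A reader might infer that lower variance brings every stopping criterion forward. It does not. Each criterion is met when "the posterior probability is greater than 95" per cent, and lower variance hastens only the one that the true effect supports: not benefit when the effect is nil or harmful, and not futility when the true difference exceeds 15%.

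What the objections do not remove: no check showed a loss of precision, no new data are needed, and the article gives no reason for the smaller set.

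**Conclusion.** The point holds as an optional improvement of low consequence. The omission is plain on the page. Its cost is roughly 0–8% of the variance of the group effect, or up to about 4% of its standard error. That range rests wholly on assumed correlations and count distributions; extreme assumed correlations would take it to about 15%.

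Three stronger readings are tempting, and the document does not support them. The first is that the primary analysis is biased or that the article contradicts itself: randomisation protects the comparison with either covariate set. The second is that the primary models adjust for own baseline alone: four further covariates are in every model. The third is that a gain of about 7% is established: that figure lies near the top of the count-simulation range. Nor is a log(1 + count) form a correction, because the article does not state the scale of the baseline, and a condensed article may leave that to the full plan.

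**What to change.** In both primary models, include the baselines of both primary outcomes, each interacted with time. Use that model at any sequential looks that remain and in the final analysis; if recruitment has closed, only the final analysis is affected. If the sponsor prefers to keep the present set, one sentence giving the reason would settle the matter.

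The cost is a few extra parameters per model in a trial of about 2000, and no new data. Because recruitment started in February 2025 and the criteria are evaluated continuously, the change needs a dated amendment made without reference to the comparative results. It should be reported with the other protocol deviations, as the article already promises under Ethics and dissemination. The own-baseline model should be kept as a sensitivity analysis. The mediator models take the same baseline variables as the primary analyses, so the amendment should say whether the change carries over to them.

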#### Models for mediators

Mediators will be explored using a causal inference framework, using Bayesian inference to estimate the natural direct effect and natural indirect effect.^75^ Mediated effects will be studied contrasting the intervention groups against each other and against the control group. One model will be estimated for each combination of outcome and mediator measure, and one model per outcome with all mediators included. Models will be adjusted for the same baseline variables as the primary analyses.

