#### Mediators

Confidence: in one’s ability to reduce drinking.Knowledge: of how to reduce one’s drinking.Injunctive norms: peer’s approval of drinking.Descriptive norms: perceptions about other’s drinking.

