### Participant timeline

In figure 1, a SPIRIT figure depicts the trial timeline. At 2 and 4 months postrandomisation, primary and mediator outcomes will be assessed to estimate the effects of immediate exposure and prolonged exposure to the interventions. The 4-month follow-up will also include a user evaluation questionnaire. At 8 months postrandomisation, all outcomes will be measured to estimate the persistent effects of the interventions. Up to three reminder texts will be sent at each follow-up interval, followed by phone calls to collect data from those not responding (maximum of five attempts).

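### The covariate set fixed for the mediation models omits the baseline mediators, leaving natural indirect effects open to confounding that randomisation does not remove

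*Protocol article*

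**What the plan says.** All references are to the protocol article.

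- **Target.** Models for mediators plans a causal mediation analysis, "using Bayesian inference to estimate the natural direct effect and natural indirect effect", for the intervention groups against each other and against control.
- **Models.** "One model will be estimated for each combination of outcome and mediator measure, and one model per outcome with all mediators included".
- **Covariates.** "Models will be adjusted for the same baseline variables as the primary analyses". Models for primary and secondary outcomes defines that set in two parts: "Models of primary outcomes will be adjusted for baseline measures of the outcome using a time-by-baseline interaction", and "all models will be adjusted for age, sex, education and access to money on short notice".
- **Mediators.** The Mediators section lists four: confidence ("Confidence: in one’s ability to reduce drinking"), knowledge, injunctive norms and descriptive norms. None of their baseline values is in the covariate set.
- **Timing.** Participant timeline states: "At 2 and 4 months postrandomisation, primary and mediator outcomes will be assessed". It continues: "At 8 months postrandomisation, all outcomes will be measured to estimate the persistent effects of the interventions". The text does not say whether mediators are also asked at baseline. The timeline figure and the questionnaire appendix, which would show this, are not available.

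The last paragraph of the Introduction names mediation as a secondary aim.

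**The concern.** Randomisation makes the groups comparable, so the effect of group on mediator and of group on outcome can be estimated without confounding. It does not make people with high and low follow-up confidence comparable within a group. Natural direct and indirect effects need that second kind of comparability, given the covariates.

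A set chosen for total effects need not supply it. Someone who is already confident at baseline, or whose peers already disapprove of heavy drinking, is likely to score similarly at follow-up and may also drink less later for that reason. Baseline drinking blocks part of this path but not all of it, if the baseline mediator also affects later drinking in its own right. The leftover association would then be credited to the intervention as mediation. Because one covariate rule covers every outcome-mediator pair and every group contrast, the same weakness would recur throughout this secondary aim.

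**Working it through.** **1. Trace the covariate set.** Models for mediators points to the primary analyses. Their set is the baseline outcome, age, sex, education and access to money on short notice. Set against the four mediators, none appears. This step rests on the text alone.

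**2. Is there a stated figure to reproduce?** No. The protocol gives no mediator stability, no mediator-outcome association and no expected indirect effect. The figures below illustrate size only, and every parameter is an assumption.

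**3. Baseline mediator as the only extra confounder.** The illustration is a linear model on a standardised scale (the planned primary-outcome models are negative binomial), with these assumptions:
- group effect on mediator a = 0.3; mediator effect on outcome b = -0.2; true indirect effect a × b = -0.06;
- correlation of baseline mediator with baseline drinking -0.3;
- s = stability of the mediator from baseline to follow-up;
- d = effect of the baseline mediator on the outcome, given the later mediator and baseline drinking.

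Given baseline drinking, the baseline mediator has variance 1 - 0.3² = 0.91. Leaving it out shifts the mediator-outcome slope by d × 0.91s / (1 - 0.09s²). The relative error in the indirect effect is that shift divided by b.

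- s = 0.3, d = -0.1: 0.273 / 0.9919 = 0.275; 0.1 × 0.275 / 0.2 = 14%.
- s = 0.7, d = -0.2: 0.637 / 0.9559 = 0.666; 0.2 × 0.666 / 0.2 = 67%.

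Simulation with 1,000,000 records agrees, to within sampling error:

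| s | d = 0 | d = -0.1 | d = -0.2 |
|---|---|---|---|
| 0.3 | -1% | 14% | 28% |
| 0.5 | 0% | 24% | 47% |
| 0.7 | 0% | 33% | 66% |

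With the baseline mediator added, every cell is within 1% of the truth. That is so by construction, since it is the only extra confounder here.

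**4. A latent trait instead.** Let an unmeasured trait drive mediator and drinking at both times, with loadings 0.2, 0.4 and 0.6. Without the baseline mediator, inflation is 39%, 110% and 158%. With it, inflation is 35%, 95% and 127%. Adjustment helps but leaves most of the bias.

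**5. Same-wave pairing with reverse causation.** Let the true indirect effect be zero, the total effect -0.2, and let drinking affect the mediator at the same wave with coefficient -0.1 to -0.3. The spurious indirect effect is 12% to 38% of the total effect without the baseline mediator, and 16% to 50% with it. With no reverse effect it is about zero. Baseline adjustment therefore does not address this separate problem.

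**The case against.** The best defence has four parts.

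- **The size is assumed.** This stands. If d is zero, so is the bias in step 3, and baseline drinking is already adjusted for. The percentages also depend on the assumed true effect: halving b doubles them, so 66% is not an upper bound, just as 0% is not excluded. A reader might infer that the indirect effects are biased, or that the baseline mediators are the strongest common causes of mediator and outcome. The documents establish neither.
- **The baseline mediator may not exist in the data.** This also stands. The text reports mediator measurement only at follow-up. If it was not collected, leaving it out is a limit of the data, not an analysis choice, and recruitment began in February 2025.
- **A condensed article leaves detail to the analysis plan.** This holds for the pairing of mediator and outcome waves. A reader might take the shared 2- and 4-month questionnaires to mean a same-wave analysis, but the protocol names no pairing, and its waves allow lagged pairs. That silence is not an error. Lagging is not a full cure either: drinking at 2 months could drive both the 2-month mediator and later drinking. The defence does not hold for the covariates, because the article states that rule, and an analysis plan could mend it only by departing from it.
- **The aim is secondary and described as exploratory.** This is correct and limits the consequence. Nor is there an error in planning single-mediator models beside an all-mediators model; which one leads is a matter of preference.

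**Conclusion.** The point holds as a weakness in a stated rule. The mediation covariates are those chosen for total effects and omit the baseline mediators, so the natural direct and indirect effects are open to mediator-outcome confounding that randomisation does not remove.

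The documents do not allow the size to be fixed. Under the assumptions in step 3, inflation of the indirect effect runs from about 0% to roughly 66%. The direction depends on the baseline mediator acting on drinking in the same direction as the later mediator; an opposite sign would shrink the estimate. Adding the baseline mediator reduces this bias where it exists but need not remove it, as step 4 shows.

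The primary effect estimates and the criteria for ending recruitment do not use the mediators and are unaffected.

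**What to change.** 1. **Covariates.** In Models for mediators, add to the primary-analysis set the baseline value of each mediator in the model, in both the mediator model and the outcome model. The all-mediators model then carries all four baseline values. This applies only if the baseline questionnaire asks for them.
2. **Sensitivity analysis.** Report how the direct and indirect effects change over a stated range of residual mediator-outcome confounding. Do this whether or not step 1 is possible. If mediators were not asked at baseline, it is the remaining remedy, and the report should say so.
3. **Advisable, not a correction.** State which waves are paired, with the mediator before the outcome: for example, the 2-month mediator with the 4-month outcome, and the 4-month mediator with the 8-month outcome. Acknowledge that earlier drinking may still drive both.

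The cost is analysis-plan wording, one extra covariate per mediator and one added analysis, with no new data. Choosing lagged pairs means giving up a same-wave mediation estimate at 2 months. The article expects a complete data set by October 2026, with analyses then, so the change can be prespecified if it is made before that.
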